#### Sample size

This has been calculated as a function of our main objective. From the hypothesis that BPSD occurs in 40% of patients [2] with a relative risk (RR) of 1.5 in relation to premorbid personality, the estimated number of subjects is 210 patients for an alpha risk of 5% and a power of 90%. With an expected drop-out rate of 20% over 3 years i.e. 42 patients, the total population required is 252 patients.

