#### Data analysis

To assess each study objectives, univariate and then multivariate analyses will be done to take into account potential confusion factors:

To evaluate the link between personality (traits and disorders) and the onset of BPSD, exploratory analyses (e.g. PCA) correlation between personality type or disorder and type of BPSD will be used.

Logistic regression models will be used for binary variables obtained from the NPI-Q and the Apathy Inventory, and linear regression models for continuous explanatory variables: intensity of the behavioural problems and total NPI-Q score.

ANOVA with repeated measures and survival models will be used to study the occurrence of these BPSD over time as seen during the various visits.

Exploratory analyses will be done to define a patient’s typology. Then, correlation between personality type and performance on social cognition tests will be assessed using linear regression models.

The link between baseline performance on social cognition tests and the risk for the onset of BPSD will be assessed with logistic regression models and survival models.

Finally, correlation between the type of BPSD and the difference in distribution of regional cerebral atrophy observed with MRI will be done using specific statistical parametric mapping (SPM) software.

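### The stated 90% power for 210 patients needs an undeclared one-sided test, a near-even exposure split and 40% as the unexposed risk; two-sided, the power is about 83%

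*Protocol article*

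**What the plan says.** The sample size is tied to the main objective, the effect of premorbid personality and life events on the risk of developing BPSD. The inputs are given in one clause: "From the hypothesis that BPSD occurs in 40% of patients [2] with a relative risk (RR) of 1.5 in relation to premorbid personality". The result follows: "the estimated number of subjects is 210 patients for an alpha risk of 5% and a power of 90"%. Drop-out is then added: "With an expected drop-out rate of 20% over 3 years i.e. 42 patients, the total population required is 252 patients".

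The section does not say whether the 5% is one- or two-sided, which group the 40% describes, or what share of the cohort counts as exposed. No other section declares a one-sided test. The Data analysis section describes exploratory and regression analyses across personality traits, personality disorders and several types of BPSD, including: "Logistic regression models will be used for binary variables obtained from the NPI-Q and the Apathy Inventory". The Discussion states a directional expectation for two traits (high neuroticism and low conscientiousness) but does not connect it to the test or to the sample size.

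**The concern.** An unqualified alpha of 5% is normally read as two-sided. On that reading the printed inputs do not lead to 210 patients at 90% power, but to about 260. The power figure is the only quantitative assurance the article gives for its main objective, and later readers will judge the study's findings, including any absence of association, against it. If the chance of missing the planned effect is 17% or more rather than 10%, that assurance is too strong.

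**Working it through.** **Inputs from the Sample size section:** risk 40%, RR 1.5, alpha 5%, power 90%, N = 210.

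**Not stated, so assumed and varied:** sidedness, exposed share, group to which the 40% belongs.

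**Formula (two proportions, pooled variance, equal groups):** n per group = [z_α·√(2·p̄(1−p̄)) + z_β·√(p0(1−p0) + p1(1−p1))]² / (p1−p0)², with z_β = 1.2816.

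**1. Reproducing 210.** Take p0 = 0.40 as the unexposed risk, p1 = 1.5 × 0.40 = 0.60, p̄ = 0.50.
- One-sided (z_α = 1.645): [1.645·√0.50 + 1.2816·√0.48]² / 0.04 = (1.163 + 0.888)² / 0.04 = 105.2 per group, 210.3 in total (212 after rounding each group up).
- Other one-sided formulae: unpooled 206, arcsine 212, log-RR 226, continuity-corrected 230. A 45% or 55% exposed share still gives 213 or 214.

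**2. The same inputs, two-sided (z_α = 1.960).** (1.386 + 0.888)² / 0.04 = 129.3 per group, so 130 per group and 260 in total. Other two-sided formulae: unpooled 254, arcsine 260, log-RR 278, continuity-corrected 280. None is near 210.

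**3. Power of 210 (105 per group).**
- Two-sided: Φ[(0.2·√105 − 1.386)/0.693] = Φ(0.958) = 83.1%.
- One-sided: Φ[(2.049 − 1.163)/0.693] = Φ(1.279) = 90.0%.
- Other two-sided tests: unpooled 84%; log-RR 81%. Log-rank, with HR = ln 0.4/ln 0.6 = 1.79 under proportional hazards and 105 events: Φ(½·√105·ln 1.79 − 1.96) = 85% (Schoenfeld), or 83% (Freedman).

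**4. Relaxing the other two conditions, N = 210.** The exposed shares are assumptions, because the article gives none. The last column sets p0 = 0.40/(1 + 0.5·share), so that the overall risk is 40%; at an even split this is 32% vs 48%.

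| Share exposed | 40% vs 60%, two-sided | 40% vs 60%, one-sided | Two-sided N for 90% (40% vs 60%) | 40% overall, two-sided |
|---|---|---|---|---|
| 50% | 83% | 90% | 260 | 66% |
| 40% | 82% | 89% | 270 | 68% |
| 30% | 76% | 85% | 308 | 65% |
| 20% | 65% | 76% | 402 | 58% |

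With 40% as the overall risk and an even split, one-sided power is 77%, and 90% two-sided needs 390 patients.

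**5. Other routes to 210.** If 1.5 were an effect per standard deviation of a trait, the two-sided requirement would be 266 (logistic) or 160 (log-risk or Cox), and the one-sided requirement 217 or 130. A one-sided log-rank calculation for HR 1.5 gives 209, but that counts events, not patients, and does not use the 40%. A two-sided continuity-corrected calculation at 80% power gives 214, but the section states 90%.

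**The case against.** **The article never says two-sided.** This is correct. A reader might infer that the arithmetic is simply wrong, but the documents do not support that: 210 follows almost exactly from the stated figures if the test is one-sided. Nor can the origin of 210 be established from the text. However, granting a one-sided test does not secure the 90%: one-sided power is 85% at 30% exposed, 76% at 20%, and 77% if 40% is the overall risk. A plan that looks across many traits, disorders and symptom types is also not a one-directional test, and the directional expectation in the Discussion covers only two traits.

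**A condensed article may leave sidedness, split and reference group to the full protocol or analysis plan.** This would answer a complaint about missing detail alone. It does not answer a printed result that disagrees with the conventional reading of its own inputs.

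**The match to 210 shows that 40% was meant as the unexposed risk.** This is plausible, and it is why 83% is the main figure here and 66% only an alternative. The words "From the hypothesis that BPSD occurs in 40% of patients" still read most naturally as the overall risk. A reader might also try 40% as the risk in the exposed, but nothing in the text supports that.

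**83% is not a hard ceiling.** This stands. Survival models are also planned, and a log-rank test reaches up to 85% under proportional hazards. If all 252 enrolled patients contributed fully, an upper bound, two-sided power would be 89% (two proportions) to 91% (Schoenfeld). The 90% is claimed for 210, however.

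**Two further inferences are not supported.** Sizing on a risk ratio and testing by logistic regression is ordinary practice, not an error, since the null hypothesis is the same. And the article does not dichotomise the NEO PI-R traits; it describes them as dimensional.

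**Conclusion.** The sentence is wrong as written, because it gives 90% without the conditions on which it depends. For a two-group comparison of risks, which is the natural reading of a relative risk, 210 patients have 90% power only with a one-sided 5% test, a near-even split and 40% as the unexposed risk together. Changing only the sidedness to the conventional two-sided 5% lowers power to about 83% (83% to 85% for the difference-in-proportions and log-rank tests; 81% on the log-RR scale) and raises the requirement to about 260 evaluable patients, more than the 252 to be enrolled. The chance of missing the planned effect is then about 17% instead of 10%, and 34% if 40% is the overall risk at an even split. The 30% and 20% exposed figures illustrate how sensitive the power is; they are not estimates of this cohort's exposed share.

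None of this shows that the design is unusable or that recruitment must rise. The stated assurance is too favourable and should be corrected.

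**What to change.** Restate the sample-size sentence, for example: *210 evaluable patients give about 83% power (two-sided 5%) to detect BPSD risks of 40% in unexposed and 60% in exposed patients, with half the patients exposed.* State explicitly the sidedness, the group to which the 40% refers and the assumed exposed share. Add the two-sided power for smaller shares (76% at 30% exposed, 65% at 20%) and for 40% as the overall risk (66% at an even split). If a one-sided test was intended, say so, give its direction and reason, and still state the split and reference risk, because the 90% depends on them.

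The cost is a rewording of one paragraph. No patients are added and study conduct does not change. The downside is a less favourable stated power.

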**Methods/Design:**

*Study type and Population*: Prospective multicentre cohort study with 252 patients with Alzheimer’s disease at prodromal or mild dementia stage.

The inclusion period will be of 18 months and the patients will be followed during 18 months. The initial evaluation will include: a clinical and neuropsychological examination, collection of behavioural symptoms data (Neuropsychiatric-Inventory scale) and their risk factors, a personality study using both a dimensional (personality traits) and categorical approach, an inventory of life events, social cognition tests and an Magnetic Resonance Imaging. Patients will be followed every 6 months (clinical examination and collection of behavioural symptoms data and risk factors) during 18 months.

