## Methods/design

### Study design

This study is a multicentre prospective cohort study of patients with Alzheimer’s disease. Patients will be followed up over a period of 18 months. At baseline visit, the patients will undergo both a clinical and neuropsychological examination, a study of their personality and important life events, social cognition and blood tests (to screen for exclusion criteria) and a brain MRI. If inclusion is confirmed, the patients will then be followed at 6-month intervals for at least 18 months.

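### The drop-out allowance adds 20% of the 210 evaluable patients instead of 20% of those enrolled, so at 20% loss 252 enrolled leaves about 202, not 210; the time base of the 20% is also unclear

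*Protocol article*

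**What the plan says.** The Sample size section of the protocol article gives the whole chain. The starting point is an event rate and an effect: "From the hypothesis that BPSD occurs in 40% of patients", "with a relative risk (RR) of 1.5 in relation to premorbid personality". From these, "the estimated number of subjects is 210 patients for an alpha risk of 5% and a power of 90" per cent. The allowance for losses follows: "With an expected drop-out rate of 20% over 3 years i.e. 42 patients, the total population required is 252 patients". The section does not state whether the test is one- or two-sided, how patients split between personality groups, or which group has the 40% rate.

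On timing, the Methods/Design part of the abstract says: "The inclusion period will be of 18 months and the patients will be followed during 18 months". The Study design section words the follow-up as a minimum: "the patients will then be followed at 6-month intervals for at least 18 months". The data collection procedures list follow-up visits at 6, 12 and 18 months and none later.

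**The concern.** The rate, the count of losses and the total are all printed, and they do not agree. A drop-out rate describes the share of enrolled patients who are lost. Here it was applied to the number meant to remain, and the result was added on. That always understates the enrolment needed.

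At stake is whether the enrolment figure delivers the evaluable number it was built to deliver. The figure is used again in the abstract and, as more than 250 patients, in the Discussion.

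The horizon is a second, separate question. The rate is tied to 3 years, while each patient's scheduled follow-up is 18 months. The section does not say how the two relate, and the answer decides whether there is any shortfall.

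**Working it through.** **Inputs.** From Sample size: evaluable number 210, drop-out 20% over 3 years, losses 42, enrolment 252, event rate 40%, relative risk 1.5. From the abstract: 18 months of inclusion plus 18 months of follow-up, 36 months in all.

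**Reproducing the plan's figure.** 0.20 × 210 = 42, and 210 + 42 = 252. The method is therefore n × (1 + d).

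**Reading A: 20% of enrolled patients are lost in total.**
- Remaining from 252: 252 × (1 − 0.20) = 201.6, about 202.
- Shortfall: 210 − 201.6 = 8.4, or 8 to 9 patients.
- Loss that 252 can bear while keeping 210: 42/252 = 16.7%.
- Enrolment needed to keep 210: n/(1 − d) = 210/0.80 = 262.5, so 263. That is 11 more than 252.

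**Reading B: 20% is a per-patient risk over 3 years, and each patient is followed for 18 months.** This needs an assumption about how the risk accrues.
- Constant hazard: 18-month loss = 1 − 0.80^(18/36) = 10.6%. Remaining: 252 × 0.894 = 225.4. Enrolment needed: 210/0.894 = 234.8, so 235.
- Linear: 18-month loss = 10%. Remaining: 252 × 0.90 = 226.8. Enrolment needed: 210/0.90 = 233.3, so 234.

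**Effect on power under reading A.** Assumptions not in the document: 40% is the reference-group rate, so the comparison is 40% versus 60% (0.40 × 1.5); the groups are equal; there is no continuity correction. With m patients per group,

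power = Φ[(0.20 − z × √(2 × 0.5 × 0.5/m)) / √((0.24 + 0.24)/m)],

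where z = 1.645 one-sided or 1.960 two-sided.

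| Evaluable | One-sided 5% | Two-sided 5% |
|---|---|---|
| 210 (m = 105) | 90.0% | 83.1% |
| 201.6 (m = 100.8) | 88.9% | 81.5% |

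The loss is 1.1 points one-sided and 1.6 points two-sided.

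Both columns are shown because the plan does not state the sidedness. Under these assumptions, 90% power needs 212 patients one-sided, close to the plan's 210, and 260 two-sided. That gap is a separate matter from drop-out.

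**The case against.** The strongest reply has three parts.

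First, the 3 years need not be an error. Inclusion plus follow-up is 18 + 18 = 36 months, so the phrase can simply mean total loss over the life of the study. This stands. A reader might infer that the plan used too long a horizon and that this adds to the shortfall. The document does not support that. If the 3 years is the study duration, no wrong rate has been used. If it is a per-patient risk, the 18-month loss is smaller than 20% and 252 leaves about 225 to 227, above 210. The horizon can only ease the problem. Nor can one say flatly that no patient is followed beyond 18 months, because the Study design section gives 18 months as a minimum. What remains is that the time base is unclear.

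Second, a patient who drops out is not wholly lost. Behavioural symptoms are recorded at each 6-month visit and survival models are planned, so someone who leaves after a visit still contributes. This stands in part. Logistic models are planned too, and the plan's own calculation treats drop-outs as lost, so the arithmetic has to be judged on that basis.

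Third, 8 to 9 patients change nothing in the design. This also stands, and it bears on how serious the point is. It does not make 252 the right result of the stated inputs.

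**Conclusion.** The point holds as an arithmetic correction of minor consequence. On the most natural reading, loss of 20% of enrolled patients, 252 gives about 202 evaluable patients instead of 210, and the matching enrolment would be 263. The cost is about 1 to 2 points of power, subject to the assumed 40% versus 60% comparison in equal groups.

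The shortfall is conditional on that reading. On the per-patient 3-year reading, with constant-hazard or linear scaling, 252 exceeds the 234 to 235 required. The section should say which reading is meant.

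A reader might also take the two-sided 81.5% as evidence that drop-out pulls the study well below its stated 90%. It does not. Most of that distance is already present at 210 (83.1%) and comes from assuming a two-sided test, which the document does not specify. Drop-out accounts for only the last 1.6 points.

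**What to change.** Keep 252 and rewrite the drop-out sentence in the Sample size section.
- State the expected loss over each patient's 18-month follow-up, and say how it relates to the 20% over 3 years.
- Then give one of two consistent statements: 252 enrolled tolerates 16.7% loss (42/252) with 210 remaining; or, at 20% loss, about 202 remain.
- Recompute the power for the evaluable number given, on the plan's own test assumptions, and print them: sidedness, split between personality groups, and the group to which the 40% applies. The percentages above should not be copied in unless those assumptions are the ones used.

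The cost is a sentence or two and one short recalculation. No extra recruitment is needed, and the design, outcomes and analyses do not change.

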#### Data analysis

To assess each study objectives, univariate and then multivariate analyses will be done to take into account potential confusion factors:

To evaluate the link between personality (traits and disorders) and the onset of BPSD, exploratory analyses (e.g. PCA) correlation between personality type or disorder and type of BPSD will be used.

Logistic regression models will be used for binary variables obtained from the NPI-Q and the Apathy Inventory, and linear regression models for continuous explanatory variables: intensity of the behavioural problems and total NPI-Q score.

ANOVA with repeated measures and survival models will be used to study the occurrence of these BPSD over time as seen during the various visits.

Exploratory analyses will be done to define a patient’s typology. Then, correlation between personality type and performance on social cognition tests will be assessed using linear regression models.

The link between baseline performance on social cognition tests and the risk for the onset of BPSD will be assessed with logistic regression models and survival models.

Finally, correlation between the type of BPSD and the difference in distribution of regional cerebral atrophy observed with MRI will be done using specific statistical parametric mapping (SPM) software.

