### Study aim and research question

#### A. Main objective

– To measure the effect of premorbid personality and life events on the likelihood of a patient with probable Alzheimer’s disease on the risk of developing BDSP.

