### Population

*Inclusion criteria are*: diagnostic criteria for AD at mild dementia stage, (NINCDS ADRDA and CDR 1) [31] or prodromal AD (CDR of 0.5) [32], age over 50 years, ability to complete the clinical and neuropsychological evaluations, and presence of a caregiver in sufficient contact with the subject to be able to note the onset of changes in behaviour.

*Exclusion criteria include*: patients with SCPD except from depression, anxiety, apathy, eating or sleep disorders at mild stage, patients with a progressive and/or poorly managed psychiatric pathology (patients with stabilised depression could be included in the study), patients taking *any* neuroleptic psychotropic medication, patients taking other psychotropic medication, with the exception of any antidepressant, hypnotic, anxiolytic, acetylcholinesterase inhibitors or Memantine which has been prescribed and stabilised for more than 3 months, and patients with serious, progressive or unstable pathologies which could interfere with the variables under consideration.

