### Outcome measures: BPSD assessment

Behavioural problems will be assessed during the initial and each subsequent consultation with the patient then by questioning his caregiver. The shortened form of the **Neuropsychiatric Inventory (NPI-Q)** and the **Apathy Inventory** will be used.

The **NPI-Q** is a questionnaire designed to collect informations on neuropsychiatric problems to patients with cerebral disorders. It is an assessment questionnaire administered to the caregiver. It is only designed to evaluate the severity of symptoms and their effect on the caregiver and not their frequency. Twelve types of neuropsychiatric symptoms are covered by the questionnaire: delusions, hallucination, agitation, depression, anxiety, euphoria, apathy, impulsive behaviour, mood swings, aberrant motor behaviour and problems with eating and sleeping.

Symptoms of apathy will also be assessed using the **Apathy Inventory**
[51]. **This** provides descriptive assessment of the form this apathy takes, from emotional indifference to lack of initiative and total disinterest in life. The information can be obtained from both the patient and his principal caregiver.

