In PACO study, we are expecting to find correlations between personality dimensions and the risk of being affected by BPSD. We hypothesize that high level of neuroticism and low level of conscientiousness will be more specifically associated with BPSD, in particular affective domains such as depression, anxiety and apathy. As cognitive decline could be positively or negatively influenced by personality, this potential association will be studied [59, 60]. Moreover, as personality development is considered to be influenced by environmental factors, childhood and adult life events will be collected to assess their possible influence on the course of AD. This would allow us, for example, to highlight the possible effects of previous exposure to a trauma or childhood deficiencies.

Subjects included in PACO study will perform a comprehensive social cognition battery including facial emotion recognition tasks. Several publications have highlighted that AD patients experience an increasing deficit in facial emotional expression recognition as the disease progresses [23], but little is known concerning the very early stage of AD [61]. Consequences of impaired facial emotion recognition on behavioral troubles in AD are questioned and should be clarified [62]. Thus, a secondary objective of the PACO study is to compare social cognition ability between MCI and mild AD, and to identify potential relationships between social cognition abilities and BPSD occurrence during the patient’s follow-up.

PACO project includes MRI 3D sequence at baseline. Different studies have linked impaired emotion recognition in psychiatric or neurologic disease to disturbances or damages of the fronto-temporal brain network [63–65]. Social cognition parameters could be correlated to initial regional cerebral volume and/or the atrophy observed one year later, which could itself be correlated to a higher risk of developing BPSD. For instance, some orbito-frontal atrophy may predict the occurrence of BPSD. Recent evidence suggests that personality traits may be related to neuroanatomical structures. Jackson et al. [66] found that higher neuroticism was associated with specific brain regions atrophy, whereas higher conscientiousness was related to larger regional volumes in healthy aging. It could be hypothesised that an interaction between personality dimension, regional brain atrophy, and BPSD may exist in AD.

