The PACO study may have several limitations. Firstly, personality should ideally have been assessed before AD onset. However, it would have been necessary to include a very large number of patients with a long follow-up. We have chosen to include patients at early stage of AD: at this stage we can suppose that the personality assessment reflects premorbid personality. Secondly, a longer follow-up would allow us to detect a larger number of BDSP. The absence of long-term follow-up could underestimate the relationship between personality and BDSP. Indeed, a certain number of SCPD increase with the evolution of the disease, but we hypothesized that some of them occur early in patients with specific personality traits. Thirdly, at baseline only patients with no or mild behavioural disturbances are selected. This inclusion methodology excludes subjects with personality dimensions associated to early behaviour disorder. Finally, the AD diagnosis was based on clinical and MRI criteria. Dubois et al. criteria refer to both imaging and to CSF markers [67]. This would allow better patient selection. However, in our centres, CSF markers are available for a small percentage of the patients, in particular when the diagnosis remains unclear. On the opposite, patients included in the PACO study had a typical clinical presentation, and CSF markers were not available for the majority of them. A systematic lumbar puncture should have limited the feasibility of our study.

The present study also has strengths. In most former studies personality assessment was performed by relatives and only a few included patients at prodromal or mild stage of AD. Moreover, to our knowledge, PACO is the first study to evaluate personality and social cognition performance and their link with subsequent BDSP.

The results of this research may help clinicians to better indentify, from a combined assessment of personality, performance in social cognition tests and the degree of cerebral atrophy, patients with AD at enhanced risk of developing BPSD and to improve patient and family care. Demonstrating a link between premorbid personality and behavioural problems will also allow us to argue for a veritable cooperation between neurologists, geriatricians and psychiatrists in the patients care throughout the course of the disease.

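### BPSD onset is not defined as incident, so symptoms already present at entry in five NPI-Q domains can be counted as onset

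*Protocol article*

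**What the plan says.** The main objective in the Protocol article (Study aim and research question, A) is incident: the effect of personality and life events "on the likelihood of a patient with probable Alzheimer’s disease on the risk of developing BDSP". The Data analysis section repeats this: "To evaluate the link between personality (traits and disorders) and the onset of BPSD".

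The Population section excludes "patients with SCPD except from depression, anxiety, apathy, eating or sleep disorders at mild stage". The limitations paragraph of the Discussion reads the rule the same way: "at baseline only patients with no or mild behavioural disturbances are selected".

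Under Outcome measures, the NPI-Q covers "delusions, hallucination, agitation, depression, anxiety, euphoria, apathy, impulsive behaviour, mood swings, aberrant motor behaviour and problems with eating and sleeping". All five symptoms tolerated at entry are on that list, and apathy is measured again by the Apathy Inventory. Table 1 marks both instruments as primary outcome measures.

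The Discussion expects high neuroticism and low conscientiousness to be linked to BPSD, "in particular affective domains such as depression, anxiety and apathy".

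On the models, Data analysis states: "Logistic regression models will be used for binary variables obtained from the NPI-Q and the Apathy Inventory". It adds linear regression for symptom intensity and total NPI-Q score, repeated-measures ANOVA, and survival models for occurrence across visits. Adjustment is described only in general terms, as multivariate analysis for potential confounders. The control variables in Table 1 are demographics, diagnosis and psychotropic medication. The GDS (current depression) is listed as an influencing factor.

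**The concern.** An analysis of onset needs patients who are free of the event at the start. The entry rule ensures this for seven NPI-Q domains but not for the other five, and the hypothesis concentrates on three of those five. As the binary variable is described, a patient with mild depression at entry and again at month 6 can be recorded as an onset.

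Personality is also assessed at baseline. Any association at that time between trait scores and current symptoms would pass through persisting symptoms into the follow-up outcome. It could then be read as a prospective effect of personality. If there is no such baseline association, the persisting cases add the same background to both groups and hide a true effect. The event rate behind the sample size is affected too, because the Sample size section does not say whether its 40% is an incident or a prevalent rate.

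**Working it through.** **Plan's own figure.** Inputs from Sample size: event rate 40%, relative risk 1.5 (read as 0.40 versus 0.60), alpha 5%, power 90%, 210 evaluable patients. Sidedness and the split between personality groups are not stated; equal groups are assumed. The pooled formula for two proportions, one-sided, gives

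n = [1.645·√(2·0.5·0.5) + 1.282·√(0.24 + 0.24)]² / 0.20² ≈ 105.2, so 106 per group, 212 in total.

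This is close to 210. The two-sided version gives 2 × 130 = 260. The power figures below are therefore given on both bases where it matters.

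**Coverage of the entry rule.** Depression, anxiety, apathy, eating and sleep may be present at mild level at entry: 5 of 12 domains. The other 12 − 5 = 7 are excluded at entry and can be new only during follow-up. The exposed outcomes are the five domains, the Apathy Inventory, and any any-BPSD or total-score outcome.

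**Model.** Let b be the share with the symptom at entry, q the share of those who still have it at follow-up, and o the onset rate in those free of it. If the binary variable is presence at follow-up, the expected rate is

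p = b·q + (1 − b)·o.

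The document gives no value for b or q, nor for o in a single domain. All are assumptions.

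**Illustration 1: no personality effect on onset.** q = 0.70 and o = 0.15 in both groups, 105 per group, unadjusted.
- b = 20%: 0.20·0.70 + 0.80·0.15 = 0.26
- b = 40%: 0.40·0.70 + 0.60·0.15 = 0.37
- Relative risk 0.37/0.26 = 1.42, where the true value is 1.
- Two-sided rejection at 5%: null SE = √(2·0.315·0.685/105) = 0.0641; alternative SE = √((0.26·0.74 + 0.37·0.63)/105) = 0.0637; (0.11 − 1.96·0.0641)/0.0637 = −0.25, so about 40%.

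With b = 10% versus 20%, the rates are 0.205 and 0.26, relative risk 1.27, rejection about 16%.

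For an any-BPSD outcome with 40% onset in both groups and b = 20% versus 40%, the rates are 1 − 0.60·(1 − 0.14) = 0.484 and 1 − 0.60·(1 − 0.28) = 0.568. The relative risk is 1.17 and rejection about 22%.

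**Illustration 2: a true effect, equal baseline prevalence.** Onset 0.40 versus 0.60, q = 0.70, 105 per group.
- b = 20%: 0.46 versus 0.62, relative risk 1.35, one-sided power 75%
- b = 40%: 0.52 versus 0.64, relative risk 1.23, one-sided power 55%

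Without persisting cases the one-sided power is 90%. The distortion can therefore go either way.

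**Cost of a symptom-free risk set.** If 20% of 210 have the symptom at entry, 210 × 0.80 = 168 remain (84 per group). At 0.40 versus 0.60, one-sided power is Φ[(0.20 − 1.645·√(0.5/84))/√(0.48/84)] = about 83%; with 1.96 in place of 1.645 it is about 74%. If 10% or 30% have it, 189 or 147 remain, with one-sided power of 87% or 79%.

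**The case against.** The strongest reply is that the article never says the binary variable means presence at a visit. The NPI-Q grades severity and entry is limited to mild symptoms, so a variable coded as new or as beyond mild would also fit the text. Coding rules and covariate lists are often left to a full protocol or analysis plan, and neither is shown here. This stands against the stronger reading, which a reader might infer, that persisting symptoms are counted as new: no section states that. It does not remove the point. What counts as an event of the main outcome is more than a coding detail when the entry rule itself admits the event, and the article does not reconcile the two.

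Adjustment is not absent either. Confounders are to be handled in multivariate models, and current depression on the GDS is an influencing factor. In Illustration 1 the spurious association disappears by construction once baseline symptom status is conditioned on, so the 40% describes the unadjusted step only. But the GDS does not cover anxiety, apathy, eating or sleep, and baseline NPI-Q and Apathy Inventory are not named for adjustment.

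The direction of bias is also uncertain. The Discussion notes that neuroticism has been linked to depression in some studies and not in others, and that people with mild disease tend to describe their former personality.

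Two further inferences are not supported. The Background and Discussion criticise earlier studies for retrospective collection, reports from relatives, small samples and late-stage disease, so this is not the same flaw repeated. Nor can heavily tied event times be held against the survival analysis, since the article names no particular survival model and no rule for ties.

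**Conclusion.** The point holds in limited form. The stated outcome is onset, the entry rule allows five of its 12 domains to be positive at the start, and the analysis section provides nothing that separates new from persisting symptoms. The weakness is confined to those five domains, the Apathy Inventory and any global or total-score outcome. The other seven domains are protected by the exclusion criteria.

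The size cannot be fixed from the article. Under the assumed inputs, a null effect on one symptom can appear as a relative risk of 1.27 to 1.42 with 16% to 40% two-sided false positives, and a true relative risk of 1.5 can shrink to between 1.35 and 1.23. These figures rest on assumed entry prevalence, persistence and single-symptom onset, equal groups, and no adjustment. They show what the wording permits, not what the study will do.

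**What to change.** Amend the Data analysis and Sample size sections as follows.
- Define onset per domain as absent at baseline and present at a later visit, and analyse it only in patients free of that symptom at baseline.
- In patients with a mild baseline symptom, analyse worsening above the baseline grade as a separate outcome, not as onset.
- Build any composite from incident events only.
- Adjust the intensity and total-score models for baseline NPI-Q or Apathy Inventory, and for the GDS.
- State whether the 40% event rate is incident or prevalent.

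The NPI-Q, Apathy Inventory and GDS are already part of the assessments, and the first two are explicitly collected at baseline, so no new measurement is needed. The cost is a smaller risk set for the affected domains: with 20% symptomatic at entry, 168 of 210 patients remain and power is about 83% one-sided or 74% two-sided. Keeping 210 at-risk patients would need 210/0.80 = 263 evaluable patients. That loss should be stated alongside the revised definition.
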